### Outcome measures

The primary outcome is the occurrence of proximal leg DVT detected 3 days or more after randomization or pulmonary embolism (PE) diagnosed on computed tomography scan (CT) of the chest or at autopsy (for definitions of outcome measures please see Additional file 5). Secondary outcomes include all other DVTs, catheter-related thrombus, anti-Xa activity, bleeding, HIT, filter lifespan, length of stay, ventilator free days, and mortality. In addition, we will monitor NGAL levels and urine volume to determine whether they can be used as prognostic factors for renal recovery.

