### Exclusion criteria

These include: a) admission diagnosis of major trauma, b) need for therapeutic anticoagulation, c) contraindication to heparin-allergy or HIT, d) pregnancy, e) life-support limitation, f) uncontrolled hypertension (blood pressure >180/110) for at least 12 hours, g) cerebral hemorrhage or acute gastrointestinal bleeding, h) severe thrombocytopenia (platelet count <50 × 109/l), i) International Normalized Ratio (INR) or activated partial thromboplastin time (APTT) more than or equal to two times the upper limit of normal, j) chronic renal failure or acute-on-chronic renal failure, and k) initial evaluation after more than 24 hours have elapsed from commencement of CRRT.

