### Examination and blood tests

Anti-Xa, activated partial thromboplastin time (APTT), platelets, D-dimer, antithrombin (AT), leukocytes, c-reactive protein (CRP), procalcitonin (PCT), hematocrit, urine and plasma NGAL, urine and plasma creatinine (Cr) are all measured at baseline. Peak and trough anti-X_a_ will be measured on day three, and once weekly. We will record the urine output prior to discontinuation of dialysis, and measure NGAL and Cr during CRRT-free intervals. All patients will have daily hematocrit and platelet count measured during the study period. Other parameters will be measured as per the departments’ norm. Samples for anti-Xa activity will be analyzed in a blinded fashion using a validated chromogenic assay kit (COAMATIC Heparin, Chromogenix, Instrumentation Laboratory Company, Lexington, Kentucky, United States). NGAL in urine and plasma will be quantified by particle-enhanced turbidimetric immunoassay (NGAL Test™, Roche Modular P apparatus, BioPorto Diagnostics A/S, Gentofte, Denmark) according to the manufacturer’s instructions.

Patients will undergo daily bedside clinical assessment for bleeding or VTE using validated tools for the ICU population [11,19,20]. Bilateral lower extremity CUS at 1-cm intervals from the iliac/common femoral vein to the popliteal vein will be conducted on the first, third, and seventh day of inclusion. CUS will then be repeated on a weekly basis (more frequently if DVT is clinically suspected). All positive CUS will be verified by a radiologist. Serial ultrasound examinations will be terminated if a positive study for DVT is obtained. Spiral pulmonary CT angiography and echocardiography will be performed on clinical suspicion of PE.

Patients will be followed until one of the following occurs: a combination of VTE and renal recovery, a combination of HIT and renal recovery, ICU death or discharge, or a change from continuous to intermittent dialysis.

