	[name]	Reviewing progress of study
	[name] [name]	Approving changes to the protocol
	[name]	Budget administration
	[name], DMSc	Advice for lead investigators
Trial management committee	[name], MB ,BS; EDIC	Decide when site visit will occur
	[name], PhD	Data verification
	[name] [name]	Randomization
	[name]	Provide annual risk report to Danish Health and Medicines
	[name] [name]	Authority and Danish national scientific ethical committee
	[name]	Serious unexpected suspected adverse events (SUSAR) reporting
	[name], DMSc	
Data manager	[name]	Maintenance of trial IT system and data verification
Data monitoring committee	[name] [name]	Review the interim analysis.
	[name] [name], PhD	Communicate the outcome of its deliberations to the Trial Steering Committee.
	[name] MD, EDIC	Independent from the sponsor and the other committees.
	[name] [name]	

We will analyze data from all randomized patients according to their assigned group (intention-to-treat principle). We will use either estimating-equation methods or continuous repeated measures (a statistical model) in the event of missing data. All baseline demographic values for these two groups will be compared, using the Student’s *t*-test or Mann-Whitney rank sum test for continuous variables and chi-squared (χ^2^) or Fisher's exact test for categorical variables.

The primary outcome VTE will be compared between the two groups. Four pre-specified subgroup analyses based on: 1) the patient's ICU admission (surgical versus medical), 2) center experience, 3) presence or absence of edema, and 4) presence or absence of vasopressor or inotropes use will be performed.

Multiple regression analysis will conducted to evaluate: 1) the influence of vasopressor, respiratory support, comorbidity, organ dysfunction scores, and CrCl on the incidence of VTE and bleeding between groups; and 2) to examine the relationship between biomarker, demographic variables, comorbidity, and Acute Kidney Injury Network classification.

The prediction ability of urine output and NGAL for successful discontinuation of CRRT will be assessed with the area under the receiver operating characteristic (ROC) curve method. Anti-Xa levels will be analyzed by repeated analysis modelling. For survival analysis, we will calculate hazard ratios and associated 95% confidence intervals using Cox regression analysis and the Kaplan-Meier method with log-rank testing.

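### The 3-day window for a primary DVT does not fit the scan schedule and the scan-stopping rule, so an early positive scan can remove a patient from the primary outcome instead of supplying an event

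*Protocol article*

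**What the plan says.** All references are to the protocol article.

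- **Outcome measures.** "The primary outcome is the occurrence of proximal leg DVT detected 3 days or more after randomization or pulmonary embolism (PE"). The PE part in full is "pulmonary embolism (PE) diagnosed on computed tomography scan (CT) of the chest or at autopsy", with no time limit clearly attached. Among the rest: "Secondary outcomes include all other DVTs, catheter-related thrombus". The section refers to Additional file 5 for definitions; that file is not shown.
- **Examination and blood tests.** Bilateral leg ultrasound "will be conducted on the first, third, and seventh day of inclusion", then weekly, or sooner on suspicion. "Serial ultrasound examinations will be terminated if a positive study for DVT is obtained". No exception is made for a scan before the 3-day cut-off. The Figure 1 legend gives the same days.
- **Modifications.** A VTE ends allocated dosing and leads to full-dose treatment, again with no exception for an early VTE.
- **Sample size and statistical methods.** "We will analyze data from all randomized patients according to their assigned group (intention-to-treat principle").
- **Exclusion criteria.** The nearest criterion is "b) need for therapeutic anticoagulation". No criterion refers to the result of a baseline scan.

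**The concern.** Each rule is reasonable alone; together they work against each other. The window keeps thrombi that were probably present at entry out of the primary outcome. But a positive scan inside the excluded period also closes the route by which that patient could later have a scan-detected primary event, while the patient still counts in the denominator.

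The day count adds a second problem. The outcome is timed from randomization and the scans from inclusion. If the third-day scan falls 2 days after randomization, a scheduled scan, early in the allocated treatment, would remove events from the primary outcome. The first scheduled scan able to supply a primary DVT would then be on day 7. Follow-up can end earlier, through ICU death or discharge or a change to intermittent dialysis, so some patients would have no qualifying scheduled scan. At stake are power and a clear coding rule for the primary endpoint.

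**Working it through.** **Step 1. Following a positive scan through the rules**

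| Scan | Days after randomization | Primary event? | Scanning stops? | In denominator? |
|---|---|---|---|---|
| First day | 0 or 1 | No | Yes | Yes |
| Third day, if day 1 is the day of randomization | 2 | No | Yes | Yes |
| Third day, if day 1 is the day after randomization | 3 | Yes | Yes | Yes |
| Seventh day | 6 or 7 | Yes | Yes | Yes |

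The first row holds under either count. The choice between rows two and three is open. Table 1 starts enoxaparin on the day of inclusion and the Figure 1 legend places dosing after randomization. This makes row two the more literal reading, but neither text defines day 1.

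**Step 2. Reproducing the planned sample size**

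Inputs (Sample size and statistical methods): control rate 40%, relative reduction 40%, hence 24% on treatment; two-sided alpha 0.05; power 80%. With pooled variance under the null and no continuity correction:

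n = [z(0.975)·√(2·p̄·(1−p̄)) + z(0.80)·√(p1(1−p1) + p2(1−p2))]² / (p1−p2)², where p̄ = 0.32

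= [1.960·√0.4352 + 0.842·√0.4224]² / 0.16² = (1.293 + 0.547)² / 0.0256 ≈ 132.3, rounded up to **133 per arm**.

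The planned figure is reproduced. Power at 133 per arm is 80.2% at alpha 0.05 and 78.9% at the final-analysis level of 0.045.

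**Step 3. Illustration of the loss**

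The documents give no rate of early positive scans. Let q be the share of patients positive before the cut-off, assumed equal in both arms. Assume also that 40% and 24% describe all randomized patients, early positives included, and that no early positive later has a PE. The primary rates become 0.40(1−q) and 0.24(1−q). For q = 5% they are 0.40 × 0.95 = 38.0% and 0.24 × 0.95 = 22.8%.

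| q (assumed) | Rates | Power, alpha 0.05 | Power, alpha 0.045 | n per arm for 80% (alpha 0.05) |
|---|---|---|---|---|
| 0% | 40.0% v 24.0% | 80.2% | 78.9% | 133 |
| 5% | 38.0% v 22.8% | 77.2% | 75.8% | 143 |
| 10% | 36.0% v 21.6% | 73.9% | 72.5% | 155 |
| 15% | 34.0% v 20.4% | 70.5% | 68.9% | 167 |

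The relative risk stays at 0.60 in every row, since both rates shrink by the same factor.

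**Step 4. Other ways to handle early positives (133 randomized per arm, alpha 0.05)**

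| q (assumed) | Non-event, as written | Left out of the analysis | Counted as event |
|---|---|---|---|
| 5% | 77.2% | 78.2% | 73.9% |
| 10% | 73.9% | 75.9% | 67.5% |
| 15% | 70.5% | 73.5% | 61.3% |

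Leaving these patients out regains 1 to 3 points. Counting them as events is worse than the present rule.

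**The case against.** The best defence is that excluding early DVT is deliberate and sound: the allocated dose cannot prevent a clot already present at entry. This stands, and Step 4 supports it. What it does not explain is why such patients stop being scanned yet remain primary non-events with no stated handling.

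The third-day scan may have been intended as the first that counts, and Additional file 5 may define the day count. This also stands, so that part is a conditional point and a request to reconcile the wording, not an established error.

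Several stronger readings are tempting, but the documents do not support them:

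- *Early thromboses disappear from the trial.* They do not. They fall under the secondary DVT outcome, and a later PE can still be a primary event.
- *Day-1-positive patients never receive the allocated dose.* The order of the first dose and the day-1 scan is not given. The Figure 1 legend mentions dosing before ultrasound, and the figure itself is not shown.
- *The comparison is biased.* A DVT present at entry is balanced in expectation by randomization. The cost in the illustration is power.
- *Power drops to near 60%.* If a quarter of events surfaced at the third-day scan and were lost, rates of 30% v 18% would give about 63% (alpha 0.05). That quarter has no source in the documents and also needs the unsettled day count. Nor does the 5–15.5% in the Background supply an entry prevalence: it describes DVT that develops despite prophylaxis.

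Finally, if the 40% planning rate was meant for the primary outcome exactly as defined, the loss in Step 3 does not follow.

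**Conclusion.** The point holds for the day-1 scan on the printed rules. A proximal DVT found then cannot be a primary event, ends the serial scans that could show one, triggers the change of treatment, and leaves the patient in the denominator with PE as the remaining route to a primary event. For the third-day scan the point is conditional on day 1 of inclusion being the day of randomization.

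The size cannot be fixed from the documents. Under assumed early-positive shares of 5–15%, equal in both arms and included in the planning rates, power falls from 80% to about 77–70% at alpha 0.05, with the relative risk unchanged. This is a worthwhile repair to make before the interim analysis. It does not show that the trial is biased or that its sample size was miscalculated.

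**What to change.** 1. **Make the third-day scan count.** Define the primary DVT as a proximal DVT first detected at or after the scheduled third-day scan, or time that scan at 72 hours or more after randomization. State how days are counted. Cost: outcome wording in an amendment, or a small shift in one scan.
2. **New patients.** Do the existing day-1 scan before randomization where feasible, so that a prevalent DVT is known when eligibility is judged. No scan is added. Cost: a possible short delay to randomization and a few patients not randomized. The 24-hour limit on initial evaluation in the exclusion criteria does not by itself grant time for this.
3. **Patients already enrolled.** Keep the all-randomized analysis. Before the interim (67 per group) and blind to arm, pre-specify an additional analysis without patients positive on the day-1 scan. The first dose may have preceded that scan, so this should accompany the intention-to-treat analysis and not replace it. Its main value is a comparison limited to patients free of DVT at entry; the gain in power is small.
4. **PE.** State whether the time window applies to it.

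The sponsor should reconcile the Modifications, Outcome measures and Examination and blood tests sections on what follows a DVT found before the cut-off. No treatment rule is proposed here.

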### Study conduct

This trial is active and enrolment began in March 2013, and will continue until March 2015. The study scheme is outlined in Figure 1. For details on the conduct of CRRT please see Additional file 6. We will record admission diagnosis, ICU severity of illness scores, and baseline demographic data for both groups of participants.

### Examination and blood tests

Anti-Xa, activated partial thromboplastin time (APTT), platelets, D-dimer, antithrombin (AT), leukocytes, c-reactive protein (CRP), procalcitonin (PCT), hematocrit, urine and plasma NGAL, urine and plasma creatinine (Cr) are all measured at baseline. Peak and trough anti-X_a_ will be measured on day three, and once weekly. We will record the urine output prior to discontinuation of dialysis, and measure NGAL and Cr during CRRT-free intervals. All patients will have daily hematocrit and platelet count measured during the study period. Other parameters will be measured as per the departments’ norm. Samples for anti-Xa activity will be analyzed in a blinded fashion using a validated chromogenic assay kit (COAMATIC Heparin, Chromogenix, Instrumentation Laboratory Company, Lexington, Kentucky, United States). NGAL in urine and plasma will be quantified by particle-enhanced turbidimetric immunoassay (NGAL Test™, Roche Modular P apparatus, BioPorto Diagnostics A/S, Gentofte, Denmark) according to the manufacturer’s instructions.

Patients will undergo daily bedside clinical assessment for bleeding or VTE using validated tools for the ICU population [11,19,20]. Bilateral lower extremity CUS at 1-cm intervals from the iliac/common femoral vein to the popliteal vein will be conducted on the first, third, and seventh day of inclusion. CUS will then be repeated on a weekly basis (more frequently if DVT is clinically suspected). All positive CUS will be verified by a radiologist. Serial ultrasound examinations will be terminated if a positive study for DVT is obtained. Spiral pulmonary CT angiography and echocardiography will be performed on clinical suspicion of PE.

Patients will be followed until one of the following occurs: a combination of VTE and renal recovery, a combination of HIT and renal recovery, ICU death or discharge, or a change from continuous to intermittent dialysis.

### Sample size and statistical methods

We hypothesized that the optimal dose of enoxaparin would reduce the incidence of VTE in critically ill AKI patients requiring CRRT without causing an increase in bleeding. An additional hypothesis was that high urine output prior to the discontinuation of dialysis and low NGAL in dialysis-free intervals can predict renal recovery in these patients.

We estimated that with 133 patients in each group the study would have 80% power to show a 40% reduction in the relative risk of VTE with 1 mg/kg enoxaparin sc QD, assuming an incidence rate of 40% in the control group, at a two-sided alpha level of 0.05. An interim analysis (for both safety and efficacy) after approximately 50% of the patients have completed the study will be performed by an independent statistician blinded to the treatment allocation. These outcomes will be analyzed with stopping rules based on the Fleming-Harrington-O’Brien stopping boundary using *P* = 0.01, with adjustment for an overall type 1 error of 0.05, and with the final analysis conducted at *P* = 0.045 [21]. The statistician will report, in strict confidence, to the DMC (see Table 3). The DMC members will not be blinded to patient allocation. They may request other analyses (such as data from other comparable trials) prior to reaching a decision on the continuation of the trial. The DMC will report its recommendations in writing to the Trial Steering Committee. The study can also be terminated if the difference between groups is negligible and the statistician using ’conditional power’ calculation determines that continuation will be futile.

**Table 3 T3:** Organizational structure and responsibilities

**Title**	**Name(s)**	**Function(s)**
Principal investigator and Research Physician	[name], MB, BS; EDIC	Design and conduct of trial F.B.I., protocol preparation and revisions, preparation of Case Report Forms, managing Clinical Trials Office, publication of study reports,member of both committees, and organization of steering committee meetings.
Lead investigators	[name], MB, BS; EDIC Odense University Hospital	Maintain trial master file and resolve contractual issues at sites
	[name], Phd	
	Svendborg Hospital	
	[name] [name] SVS Esbjerg Hospital	Responsible for identification, recruitment, data collection, and completion of CRFs, along with follow-up of study patients and adherence to study protocol.
Steering committee	[name], MB ,BS; EDIC	Agreement of final protocol
	[name]	Reviewing progress of study
	[name] [name]	Approving changes to the protocol
	[name]	Budget administration
	[name], DMSc	Advice for lead investigators
Trial management committee	[name], MB ,BS; EDIC	Decide when site visit will occur
	[name], PhD	Data verification
	[name] [name]	Randomization
	[name]	Provide annual risk report to Danish Health and Medicines
	[name] [name]	Authority and Danish national scientific ethical committee
	[name]	Serious unexpected suspected adverse events (SUSAR) reporting
	[name], DMSc	
Data manager	[name]	Maintenance of trial IT system and data verification
Data monitoring committee	[name] [name]	Review the interim analysis.
	[name] [name], PhD	Communicate the outcome of its deliberations to the Trial Steering Committee.
	[name] MD, EDIC	Independent from the sponsor and the other committees.
	[name] [name]	

We will analyze data from all randomized patients according to their assigned group (intention-to-treat principle). We will use either estimating-equation methods or continuous repeated measures (a statistical model) in the event of missing data. All baseline demographic values for these two groups will be compared, using the Student’s *t*-test or Mann-Whitney rank sum test for continuous variables and chi-squared (χ^2^) or Fisher's exact test for categorical variables.

The primary outcome VTE will be compared between the two groups. Four pre-specified subgroup analyses based on: 1) the patient's ICU admission (surgical versus medical), 2) center experience, 3) presence or absence of edema, and 4) presence or absence of vasopressor or inotropes use will be performed.

Multiple regression analysis will conducted to evaluate: 1) the influence of vasopressor, respiratory support, comorbidity, organ dysfunction scores, and CrCl on the incidence of VTE and bleeding between groups; and 2) to examine the relationship between biomarker, demographic variables, comorbidity, and Acute Kidney Injury Network classification.

The prediction ability of urine output and NGAL for successful discontinuation of CRRT will be assessed with the area under the receiver operating characteristic (ROC) curve method. Anti-Xa levels will be analyzed by repeated analysis modelling. For survival analysis, we will calculate hazard ratios and associated 95% confidence intervals using Cox regression analysis and the Kaplan-Meier method with log-rank testing.

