**Discussion:**

Critically ill unit patients with acute kidney injury present a particular challenge in the provision of thromboprophylaxis. This study hopes to add to the growing evidence that the existing recommendation of 40 mg enoxaparin is inadequate and that 1 mg/kg is both safe and effective for thromboprophylaxis.

In addition, the study seeks to identify predictors of renal recovery allowing for the proper utilization of resources.

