## Methods/Design

### Trial design

This is a multicenter randomized controlled trial conducted at three ICUs across Denmark to assess whether a dose of 1 mg/kg enoxaparin versus standard dose of 40 mg enoxaparin will improve thromboprophylaxis in AKI patients on CRRT, without increasing the risk of bleeding. We will randomly assign eligible critically ill adults with AKI into a treatment arm (1 mg/kg enoxaparin sc QD) or a control arm (40 mg enoxaparin sc QD) upon commencement of CRRT. The sample population will consist of 133 patients from ICUs at Odense University Hospital (OUH), Svendborg Hospital, and SVS Esbjerg Hospital. An interim analysis will be conducted after the first 67 patients have been included in each group. Enrolment began in March 2013 and will continue until March 2015. Patients will be followed until either: (1) a combination of VTE and renal recovery, (2) a combination of heparin - induced thrombocytopenia (HIT) and renal recovery, (3) ICU death or discharge, or (4) change from continuous to intermittent dialysis. Investigators will obtain consent for the collection of data on treatments and outcomes for participants who withdraw prematurely from the project. Many of the current investigators have participated in other trials and, as such, have a proven track record with respect to enrolment and follow-up of participants and collecting complete data sets. We will document the reasons for missing data, collect auxiliary variables that may predict outcome and/or determine which patients are more susceptible to dropout, and follow-up on all such patients until 24 hours after the last dose of enoxaparin.

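### The interim P = 0.01 efficacy boundary is also applied to safety, and the hypothesis of no increase in bleeding has no margin

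*Protocol article*

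**What the plan says.** Under Sample size and statistical methods, the hypothesis is that the optimal dose "would reduce the incidence of VTE in critically ill AKI patients requiring CRRT without causing an increase in bleeding". Trial design gives the same double aim: whether the higher dose "will improve thromboprophylaxis in AKI patients on CRRT, without increasing the risk of bleeding". The abstract's Discussion hopes to support the view that "1 mg/kg is both safe and effective for thromboprophylaxis".

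The sample size rests on venous thromboembolism (VTE) alone: "with 133 patients in each group the study would have 80% power to show a 40% reduction in the relative risk of VTE", "assuming an incidence rate of 40% in the control group, at a two-sided alpha level of 0.05". Bleeding is listed among the secondary outcomes in Outcome measures.

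The interim is described as "An interim analysis (for both safety and efficacy) after approximately 50% of the patients have completed the study". The text continues: "These outcomes will be analyzed with stopping rules based on the" Fleming-Harrington-O'Brien boundary at P = 0.01, with the final analysis at P = 0.045. Elsewhere the interim is placed at 67 patients per group. No separate threshold for safety, and no tolerable excess of bleeding, appears in the article.

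The same section says that the DMC is not blinded to allocation, may ask for further analyses before deciding, and makes its recommendation in writing to the steering committee.

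**The concern.** Two things are fixed in a way that does not suit a harm outcome.

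- **The interim boundary.** A threshold of P = 0.01 at half the information exists to keep the overall chance of a false efficacy claim at 5%. Stopping because of excess bleeding leads to no efficacy claim, so it cannot inflate that error. Applied to bleeding, the strictness makes the formal rule slower to flag an excess and protects nothing in return.
- **The final claim.** A hypothesis of no increase cannot be supported by a non-significant difference alone. Without a margin, the only yardsticks in the text are P values, and the trial was sized for a different outcome. If bleeding is uncommon, a real excess could coexist with a non-significant test.

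The Background says these patients are predisposed to bleeding, and the closing Discussion expects the results to challenge the avoidance of selected low-molecular-weight heparins. The safety half of the conclusion therefore carries weight.

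**Working it through.** **1. The plan's own figures.** VTE 40% v 24% (40% × 0.6), two-sided 0.05, 80% power, pooled variance, mean rate 0.32:

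n = [1.96·√(2·0.32·0.68) + 0.8416·√(0.40·0.60 + 0.24·0.76)]² / 0.16² = 132.2, so 133 per arm.

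This reproduces the stated number. P = 0.01 at half information followed by P = 0.045 gives an overall two-sided error of 0.0498 (bivariate normal, correlation √0.5). Neither figure is in dispute.

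**2. Inputs for bleeding.** From the documents: 67 per arm at P = 0.01; 133 per arm at P = 0.045. Control bleeding rate: not given, so a range is assumed. Test: pooled two-proportion z-test, exact enumeration over binomial counts, counting only an excess in the treated arm.

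**3. Probability that a doubling reaches the stated threshold.**

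| Assumed control v treated rate | Interim, 67 per arm, P = 0.01 | Final, 133 per arm, P = 0.045 |
|---|---|---|
| 2% v 4% | 0.5% | 13% |
| 5% v 10% | 6% | 32% |
| 8% v 16% | 12% | 50% |
| 10% v 20% | 16% | 62% |
| 15% v 30% | 31% | 83% |
| 20% v 40% | 48% | 95% |

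Hand check of the 5% v 10% final entry: pooled standard error √(2·0.075·0.925/133) = 0.0323; unpooled √((0.05·0.95 + 0.10·0.90)/133) = 0.0322; (0.05 − 2.005·0.0323)/0.0322 = −0.46; Φ(−0.46) = 0.32.

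Detection passes 50% at a control rate of about 20.5% at the interim and about 8.0% at the end.

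**4. What a looser harm threshold would do at 67 per arm.**

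| Assumed rates | Two-sided 0.01 | Two-sided 0.05 | One-sided 0.05 |
|---|---|---|---|
| 5% v 15% | 25% | 51% | 64% |
| 5% v 10% | 6% | – | 30% |

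With equal rates in both arms, one-sided 0.05 gives a false alert about 4% of the time at 2% and 6% at 5%.

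**5. What 133 per arm can exclude.** Half-width of the 95% CI for the risk difference with equal rates p is 1.96·√(2p(1−p)/133): 3.4 points at 2%, 5.2 at 5%, 7.2 at 10%.

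Illustration: 7 v 14 bleeds of 133 is a difference of 5.3 points, P = 0.11, 95% CI −1.2 to +11.7 points. The test is non-significant, yet the interval includes more than a doubling.

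To exclude a 5-point excess (one-sided 0.025, 80% power, no true difference), n = (1.96 + 0.8416)²·2p(1−p)/0.05²: 299 per arm at 5% and 566 at 10%.

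**The case against.** A reader might infer that bleeding is judged by significance tests alone, that a doubling would usually pass as safe, and that enrolment would continue through a clear excess. The documents do not support these readings.

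- **No stated rule equates non-significance with safety.** The abstract expresses a hope, and the closing Discussion confines its claim of class I evidence to the primary endpoint.
- **The boundary is not the only safeguard.** An independent, unblinded DMC with intensive-care, thrombosis and statistical members may ask for more before it recommends. Serious adverse events go to the sponsor at once, bleeding is assessed daily, and a regression analysis also covers bleeding.
- **Whether a doubling is usually missed depends on the rate.** From 10% upward, the final analysis usually detects it. The Background calls major or fatal bleeding very rare, but the listed outcome is bleeding in general, which could be more frequent.
- **Documents not shown.** The bleeding definitions are in Additional file 5, the DMC works under its own charter, and an analysis plan may set a margin. Sizing a trial on its primary efficacy outcome is ordinary practice.

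All of this stands and limits the point. It does not remove the stated rule: the article places safety under the P = 0.01 boundary and does not say that the DMC may act on harm short of it. Discretion to ask for other analyses is not a harm guideline.

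**Conclusion.** The point holds in a limited form. The article fixes an efficacy-type boundary for safety and pairs a no-increase hypothesis with P thresholds and no margin.

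At the interim, a doubling of bleeding would more often than not fail to reach P = 0.01 for any control rate below about 20%. At the final analysis, it is more likely missed than found only below about 8%. That is plausible for major bleeding and not established for bleeding of any grade.

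These sizes rest on assumed rates, on a doubling as the excess of interest, and on a pooled z-test with the planned numbers completed. Fisher's test would be somewhat stricter at the interim: with 3 control bleeds it needs 14 treated bleeds for P < 0.01, against 13 with the z-test. The sample size for VTE and the 0.01/0.045 split are sound. This should be corrected, but it does not threaten the primary efficacy analysis.

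**What to change.** 1. In Sample size and statistical methods, limit the P = 0.01 boundary to efficacy and state that the DMC's judgement on harm is not bound by it.
2. Give the DMC a separate, looser, non-binding statistical guideline for bleeding, for example one-sided 0.05, and make the wording agree with the DMC charter.
3. Report bleeding as a risk difference with its 95% CI. Claim no increase only if the upper limit is below a margin set in advance by the steering committee; otherwise call the result inconclusive and give the interval. If Additional file 5, the charter or an analysis plan already holds a margin or harm rule, bring this section into line with it.

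**Cost.** Wording only: no added patients and no efficacy alpha spent. The example guideline carries about a 4–6% chance of a false alert and is no complete cure, since it flags 5% v 10% only about 30% of the time at 67 per arm. With a CI half-width of about 5 points at a 5% rate and 7 points at 10%, the safety claim will often end as inconclusive. That is the honest reading of what 266 patients can show.
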